#### Health economics

Data on healthcare utilisation will be collected but not analysed. To answer the feasibility questions related to the health economic perspectives, we will test the completion of the health resource use questionnaire and will present the data descriptively.

#### Data management

All data will be processed according to the Data Protection Act 2018^23 34 35^ and all documents will be stored safely in confidential conditions. Trial-specific documents, except for the signed consent form and contact details, will refer to the participant with a unique study participant number and initials only. Participant identifiable data will be stored separately from trial data.

### Qualitative investigation

The embedded qualitative study will assess the feasibility and acceptability of the experimental and control interventions from the perspectives of those delivering (physiotherapists) and receiving (participants) the interventions. The format and delivery of the qualitative interviews are based on parameters successfully implemented in previous trials conducted by the research team (Back Skills Training Trial (BeST),^36^ Better Outcomes for Older people with Spinal Trouble Trial (BOOST),^21^ The Prevention of Shoulder Problems Trial (PROSPER),^37^ Strengthening and Stretching for Rheumatoid Arthritis of the Hand Trial (SARAH)^38^), and UK trials involving cancer patients.^39^ Specifically, participant opinion and experience of study recruitment, intervention content, timing and accessibility and barriers and facilitators to adherence will be sought. Qualitative themes identified will be used to modify the content and delivery of a future definitive trial.

#### Recruitment

Fifteen participant interviews will be conducted, involving 10 participants from the experimental intervention group and five from the control group. Based on our previous trial work,^36 38^ this sample size is expected to ensure data saturation across both groups, allowing for the expected larger dataset from the experimental intervention group.

All participants will be given a brief explanation of the interviews during the initial consent process. Those willing to be interviewed will indicate permission to be contacted by the qualitative researcher on the Consent Form (online supplemental file 1). It will be clarified that not all willing participants may be required for the interview study.

Participants who have agreed to be contacted for the interview will be purposively sampled by the qualitative researcher to ensure the 15 interview participants are demographically representative of the full study sample. Targeted demographics include age, ethnicity, employment status and extent of ND. We estimate that the sample will include more males than females because approximately 70% of HNC cases in the UK in males.^40^ We aim to invite two males for every one female we interview. However, if we are restricted in the number of participants available for interview, we will interview as many as available. We will highlight the sex of participants as part of our interpretation of our qualitative analysis.

The qualitative researcher will telephone the sampled participants, and answer any questions they may have about taking part in the interviews. If the participant agrees to take part, a time and date convenient to the participant will be arranged for an interview. Interviews will be conducted face to face, and occur at a location convenient to the participant, most likely in their own home.

A minimum of one physiotherapist who delivered the experimental intervention and one physiotherapist who delivered the control intervention will be interviewed from each site, until data saturation is reached. This is anticipated to occur within a maximum of 12 interviews. Each physiotherapist will be asked to read the clinician qualitative study PIS, and then to complete a consent form (online supplemental file 2). Physiotherapists who consent to participate will be contacted to arrange a suitable time to conduct a telephone interview.

10.1136/bmjopen-2020-045741.supp2Supplementary data

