#### Delivery

The experimental intervention will be delivered a maximum of six sessions over a 6-month period. The design will enable assessment of how many sessions are required. The first session will aim to occur within 14 days of surgery. Reflecting normal NHS practice, the initial session will be 60 min, and subsequent sessions up to 45 min in duration. The physiotherapist, in collaboration with the participant, will agree the spacing of sessions, reflecting normal clinical practice. This spacing will allow for maximum progression of the intensity of exercise over a time period sufficient to (hypothetically) produce an improvement in outcome. Treatment options may also be added or removed at each session, in line with the participant’s current treatment progress and health status.

The timing and spacing of sessions around additional treatments such as radiotherapy and chemotherapy will be determined by the participant and physiotherapist. Through this, if the participant or physiotherapist feel that the intervention is not appropriate due to radiotherapy/chemotherapy side effects such as fatigue, pain or nausea, the GRRAND intervention will be delayed until symptoms reduce. Alternatively, if the participant and physiotherapist agree that the GRRAND intervention would be beneficial alongside such treatments, this will be permitted. This reflects the individualised nature of the intervention.

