#### Data collection

Interviews will be conducted 4–6 weeks after a participant’s final physiotherapy session. This cross-sectional time point allows exploration of the participant’s study experience and adherence to home exercise in a reasonable recall period. Participant interviews will take up to 90 min. The physiotherapist interviews will take 15–30 min and will be completed within 4 weeks of intervention completion.

We conducted a brief literature review of evidence into the biopsychosocial barriers and facilitators for this patient group to return to their daily activities with acceptable quality of life. In parallel, we attended HNC patient rehabilitation groups to deepen our understanding of the patient perspective. The themes identified from the literature review and patient groups informed the semistructured interview guide and framework. The qualitative researcher presented these to our PPI representatives and clinical experts and refined accordingly. The refined interview guide is provided in online supplemental file 3. The interview schedule will be structured in alignment with the guidance for the qualitative exploration of intervention acceptability recently published in the BMJ.^41^ Interviewees will have the opportunity to suggest and/or discuss additional questions. Interviews will be audio recorded, and independently transcribed.

10.1136/bmjopen-2020-045741.supp3Supplementary data

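### Interviews meant to explain adherence are neither sampled on attendance nor timed for people who stop early, so early stoppers risk being under-represented

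*Protocol article*

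**What the plan says.** The Qualitative investigation section of the protocol article gives the purpose of the patient interviews. Among other topics, "barriers and facilitators to adherence will be sought", and the resulting themes are to guide changes to the content and delivery of a definitive trial. Table 1 uses the interviews, together with attrition and non-attendance rates, to judge feasibility and acceptability.

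The Recruitment subsection sets the numbers: "Fifteen participant interviews will be conducted, involving 10 participants from the experimental intervention group and five from the control group". The frame is formed at consent: "Those willing to be interviewed will indicate permission to be contacted by the qualitative researcher on the Consent Form". From that frame, participants are purposively sampled "to ensure the 15 interview participants are demographically representative of the full study sample". The named factors are these: "Targeted demographics include age, ethnicity, employment status and extent of ND". An aim of two men for every woman is added.

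The Data collection subsection fixes the timing: "Interviews will be conducted 4–6 weeks after a participant’s final physiotherapy session". The reason given is that "This cross-sectional time point allows exploration of the participant’s study experience and adherence to home exercise in a reasonable recall period". The Abstract places the invitation elsewhere, when people finish taking part in the study.

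Under Intervention, Delivery, the programme is "a maximum of six sessions over a 6-month period". Spacing is agreed between participant and physiotherapist, and sessions may be put off while side effects of radiotherapy or chemotherapy last.

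**The concern.** People who stop attending are the ones best placed to say why the programme was hard to follow. Two features of the plan work against hearing them.

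First, nothing in the sampling depends on attendance, so a set of ten experimental-arm interviewees could match the trial sample on every named factor and contain no early stopper.

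Second, the timing rule suits people whose last session is planned. A person who drops away without notice has a last session that becomes final only with hindsight. The article has no rule for when that happens.

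If interviewees are mostly people who completed, the themes will lean towards acceptance, and those themes feed directly into the design of the definitive trial.

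**Working it through.** **The plan's own figure.** 10 experimental + 5 control = 15 interviews, as stated. No power or precision formula applies. The check is on who can reach the interview.

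**Step 1: time left in the window.** The window closes 6 weeks after the last attended session. If a stop is first noticed at the next missed appointment, the time left is 6 minus the session spacing in weeks. The article does not give the spacing, so a range is shown.

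| Assumed spacing (weeks) | Weeks left in the window |
|---|---|
| 2 | 4 |
| 4 | 2 |
| 5.2 | 0.8 |
| 6 or more | none |

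The 5.2 is 26 weeks / 5 intervals. It assumes that all six sessions are used and spread evenly, which the plan does not say. Because pauses are allowed, one absence need not mean stopping. If two missed appointments are needed, 4-week spacing gives 2 × 4 = 8 weeks, which is past the 6-week limit.

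**Step 2: how early the window can close.** Take a programme of about 26 weeks. If the last attended session is in week 2, 6 or 10, the window closes in week 8, 12 or 16. That is 18, 14 or 10 weeks before the programme period ends, so further sessions could still be expected when it closes.

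**Step 3: what this could do to the sample.** Inputs from the article: 30 participants per arm (Sample size) and 10 experimental interviews. Assumption: *s* of the 30 stop early. The article gives no stopping rate.

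If selection is unrelated to stopping, the expected number of stoppers is 10 × *s*/30 and P(none) = C(30 − *s*, 10) / C(30, 10).

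If each stopper has relative weight *w* of being selected and reached (a further assumption), draws are made one at a time and P(none) is the product over *i* = 0 to 9 of (30 − *s* − *i*) / (30 − *s* − *i* + *w* × *s*). The expected numbers come from the corresponding Wallenius non-central hypergeometric distribution.

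| Stopping early | Neutral: expected; P(none) | *w* = 0.25: expected; P(none) | *w* = 0.1: expected; P(none) |
|---|---|---|---|
| 3 of 30 (10%) | 1.0; 0.28 | 0.3; 0.72 | 0.1; 0.87 |
| 6 of 30 (20%) | 2.0; 0.065 | 0.7; 0.47 | 0.3; 0.73 |
| 9 of 30 (30%) | 3.0; 0.012 | 1.1; 0.27 | 0.5; 0.58 |
| 15 of 30 (50%) | 5.0; <0.001 | 2.4; 0.04 | 1.2; 0.24 |

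Demographic sampling alone does not push stoppers out. It also guarantees none. Any loss would come from the timing rule and from difficulty in reaching people, and no sampling factor is there to offset it.

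**The case against.** A reader might infer that early stoppers are systematically missed, or that their final session is unknown. The article supports neither reading. Permission to be contacted is taken at consent, before anyone can stop, and no attendance condition is attached, so stoppers stay in the frame. Neutral selection would draw them in proportion. Table 2 lists a physiotherapist-completed log, so the last attended session can be found in retrospect. What is missing is only a rule for when it counts as final.

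Other points also stand:

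- The tight window affects people who stop without saying so. Someone who tells the physiotherapist is known at once, and with short early gaps a missed appointment shows before the window opens.
- The list of factors is worded as open, and extent of neck dissection is a clinical factor. The fuller protocol may say more.
- A 30% stopping rate cannot be taken from Table 3. With 9 of 30 non-compliant, compliance is exactly 70%, which is Amber, because Green needs more than 70%. Six sessions is also a maximum, so attending fewer may be compliant.
- No progression criterion in Table 3 depends on what interviewees say.
- Logs, non-attendance rates, home exercise diaries and physiotherapist interviews also bear on adherence, and the framework is to be triangulated with quantitative data.

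The last point does not remove the problem. Logs and rates count absences without giving patients' reasons, and a physiotherapist's account of why a patient left is second-hand. Nor is this only a matter of detail held elsewhere: the article itself states the sampling aim and the interview window, and these fit its stated purpose poorly.

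**Conclusion.** The point holds as a risk of under-representation. The interviews are to explain adherence, the stated sampling has no protection for early stoppers, and the stated window can be nearly over or past before a silent stop is recognised.

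The size cannot be fixed from the article. It depends on the stopping rate, the session spacing and how hard stoppers are to reach, none of which is given. Under the assumptions shown, at 20% to 30% stopping the chance of hearing no early stopper runs from 0.065 to 0.012 with neutral selection, and from 0.73 to 0.58 if stoppers are a tenth as likely to be selected and reached. The consequence is confined to the qualitative evidence that will shape the definitive trial. The change is cheap and worth making.

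**What to change.** 1. In the qualitative Recruitment subsection, add attendance status from the physiotherapy log (completed as agreed with the physiotherapist, stopped early, did not attend) as a purposive sampling factor for the 10 experimental-arm interviews. State a minimum number of early stoppers where available. Three of 10 is one example: it is the proportional share if 30% stop, which is an assumption.
2. In the qualitative Data collection subsection, keep the 4 to 6 week window for those who complete. For early stoppers, allow the interview at any time after stopping is recorded, and say when an unplanned last session counts as final.
3. Reconcile the Abstract, which places the invitation at the end of study participation, with the Data collection subsection.

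The number of interviews stays at 15 and the attendance data are already logged. The price is slightly looser demographic matching and longer recall for some interviewees.

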#### Data collection

Interviews will be conducted 4–6 weeks after a participant’s final physiotherapy session. This cross-sectional time point allows exploration of the participant’s study experience and adherence to home exercise in a reasonable recall period. Participant interviews will take up to 90 min. The physiotherapist interviews will take 15–30 min and will be completed within 4 weeks of intervention completion.

We conducted a brief literature review of evidence into the biopsychosocial barriers and facilitators for this patient group to return to their daily activities with acceptable quality of life. In parallel, we attended HNC patient rehabilitation groups to deepen our understanding of the patient perspective. The themes identified from the literature review and patient groups informed the semistructured interview guide and framework. The qualitative researcher presented these to our PPI representatives and clinical experts and refined accordingly. The refined interview guide is provided in online supplemental file 3. The interview schedule will be structured in alignment with the guidance for the qualitative exploration of intervention acceptability recently published in the BMJ.^41^ Interviewees will have the opportunity to suggest and/or discuss additional questions. Interviews will be audio recorded, and independently transcribed.

10.1136/bmjopen-2020-045741.supp3Supplementary data

#### Data analysis

Transcriptions will be managed using NVIVO software.^42^ Qualitative researcher (BF) will analyse the data using framework analysis.^43^ The analytical framework will be informed by our evidence synthesis of the biopsychosocial rehabilitation and behaviour change literature and refined through consultation with PPI and clinical experts. After the coding of each transcript the working framework will be discussed with patient, clinical and research team members to reduce researcher bias and strengthen the framework’s reliability. The final framework will include data from participants and physiotherapists and will be triangulated with quantitative data. We will produce and publish a framework of understanding for the intervention and trial progression.

### Trial status

The trial is funded for 24 months commencing in September 2019. Recruitment is expected to be complete by October 2020 with the final follow-up visit completed by April 2021. The trial will be completed by 31 August 2021. Due to the COVID-19 outbreak in the UK from March 2020, the trial timelines are expected to be extended.

### Protocol changes resulting from COVID-19

The protocol was amended to reflect the NHS service delivery changes secondary to COVID-19. These amendments include allowing intervention delivery to have the option of video consultations in line with local NHS Trusts’ policies. The change to online consultations has been reflected in the addition of eligibility criterion ‘When the hospital is only providing video consultation physiotherapy sessions, does the patient have access to the internet through a computer or tablet’. Video-delivered interventions will be monitored via video link using NHS software. Qualitative interviews will now be conducted via telephone for both patients and physiotherapists.

Follow-up data collection via telephone, and postal questionnaire data collection options have been added to minimise the need for participant hospital attendance. The study team will attempt to contact these participants on up to two occasions to remind them to complete the questionnaires. If these methods fail, we will categorise the participant as a ‘non-responder’ for that time point only. Qualitative data will now be collected using telephone interviews for all groups.

We plan to recruit an additional three participants to replace the participants recruited pre-COVID who were unable to adhere to the intervention due to the emergency changes in service provision.

### Patient and public involvement

Patient involvement began during protocol and intervention development and continues throughout the trial. A patient-member will attend all TSC meetings. The same patient member is a coinvestigator, providing insights into the trial conduct, particularly on data collection processes, and will help interpret the findings to inform on the implications of the research during the trial’s dissemination phase.

## Ethics and dissemination

Ethical approval was gained from the South Central (Oxford B) Research Ethics Committee. A TSC was appointed to independently review the data on safety, protocol adherence and recruitment to the trial. Direct access will be granted to authorised representatives from the sponsor and host institution for monitoring and/or audit of the trial to ensure compliance with regulations. Anonymised data will be shared outside the research team when required. Researchers outside the trial team may formally request for a specific data set as per the Data Management Plan. All requests will need to be approved by the TMG.

Reporting of the trial will be consistent with the Consolidated Standards of Reporting Trials 2010 Statement and its various extensions (pilot and feasibility trials, patient reported outcomes and non-pharmacological interventions)^44^ and Template for Intervention Description and Replication guidelines.^45^ A summary of the results and trial materials will be made available via the trial website on completion of the trial. We will submit the final report to a peer-reviewed academic journal.
